## Abstract

**Background:**

Children commonly present to Emergency Departments (ED) with a non-blanching rash in the context of a feverish illness. While most have a self-limiting viral illness, this combination of features potentially represents invasive serious bacterial infection, including meningococcal septicaemia. A paucity of definitive diagnostic testing creates diagnostic uncertainty for clinicians; a safe approach mandates children without invasive disease are often admitted and treated with broad-spectrum antibiotics. Conversely, a cohort of children still experience significant mortality and morbidity due to late diagnosis. Current management is based on evidence which predates (i) the introduction of meningococcal B and C vaccines and (ii) availability of point of care testing (POCT) for procalcitonin (PCT) and *Neisseria meningitidis* DNA.

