#### Lamp md

LAMP-MD is a rapid molecular amplification test for the detection of all serogroups of *N. meningitidis* DNA. It can be performed in the ED on a bench top analyser and provides results within 30 min (Fig. 1). Initial testing has shown that LAMP-MD has superior sensitivity (0.89 [95%CI 0.72–0.96]) and specificity (1.0 [95%CI 0.97–1.0]) in diagnosing MD than traditional tests (C-reactive protein [CRP] and White Blood Cell counts [WBC]) recommended by NICE [10, 11]. The LAMP-MD test is now available commercially and is CE-IVD approved. The test performs equally well on blood samples and throat swabs, [10] with results available more quickly from throat swabs due to a shorter and simpler DNA extraction process.

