## Methods/design

As a diagnostic accuracy study our Petechiae in Children (PiC) study adheres to the STARD criteria for the reporting of diagnostic accuracy studies [13]. The gold standard test against which our outcomes are measured is quantitative PCR (qPCR) for *N. meningitidis* DNA in a sterile body site (blood or CSF). Or confirmation of an invasive bacterial infection through positive culture or qPCR of a bacterial pathogen.

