### Objectives

The co-primary outcomes are the diagnostic accuracy (sensitivity, specificity, positive predictive value, and negative predictive value) of:POCT for (i) *N. meningitidis* DNA and (ii) PCT in the diagnosis of MD in children with fever and NBRPOCT for *PCT* in the diagnosis of Invasive bacterial infection

Secondary objectives:Evaluate the performance accuracy of existing CPGs in identifying MDEvaluate cost-effectiveness of available diagnostic testing strategiesExplore views of (i) families and (ii) clinicians on research without prior consent (RWPC) using qualitative methodologyReport on the aetiology of NBRs in children with a feverish illness

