### Reference standards

In all cases of possible MD, blood and/or CSF is tested for *N. meningitidis* DNA using quantitative crtA TaqMan PCR using standard UK laboratory methods. The reference standard test is performed by staff blinded to the result of the index test. A positive reference standard test will be used to give a diagnosis of “confirmed MD”.

In cases where the diagnosis is unclear or where the child has been diagnosed as “probable MD” by the clinical team but where the reference standard test is negative a committee of clinicians will review the anonymised medical records blinded to results of POCT and decide if the case can be given the diagnosis of “probable MD”.

For other invasive bacterial infections, the reference standard test is positive culture or qPCR of bacterial pathogen from a sterile body site (blood/CSF) performed by staff blinded to the result of the index test.

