### Statistical analysis

In keeping with the objectives we will report:

Primary:The diagnostic accuracy of POCT for (i) *N. meningitidis* DNA and (ii) PCT in the diagnosis of early MD against the reference standard (qPCR) for *N. meningitidis* DNA in blood/CSF). The sensitivity, specificity, NPV and PPV will be reported.The diagnostic accuracy of POCT for *PCT* in the diagnosis of early invasive bacterial infection against the reference standard of positive culture from a sterile site (blood/CSF). The sensitivity, specificity, NPV and PPV will be reported.

Secondary:The diagnostic accuracy of existing UK guidance in the diagnosis of early MD against the reference standard qPCR) of blood/CSF. The sensitivity, specificity, NPV and PPV will be reported. McNemar’s test will be performed to determine the significance in performance of different guidance. Where possible the effect of incorporating POCT into existing guidance will be explored and reported in term of sensitivity, specificity, NPV and PPV.Report on the aetiology of NBRs in children with a feverish illnessThe epidemiology of the population of children who present with fever and a NBR

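### The case definition of the second co-primary (PCT for invasive bacterial infection) differs between sections, and read literally it counts qPCR-confirmed, culture-negative meningococcal disease as disease-free

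*Protocol article*

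**What the plan says.** Four places in the protocol article bear on who counts as diseased in the second co-primary.

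- **Abstract, Background.** Fever with a non-blanching rash "potentially represents invasive serious bacterial infection, including meningococcal septicaemia". MD is a member of the wider class.
- **Methods/design.** After naming qPCR for *N. meningitidis* as the gold standard, it adds: "Or confirmation of an invasive bacterial infection through positive culture or qPCR of a bacterial pathogen". Either method suffices, and *N. meningitidis* is not excepted.
- **Reference standards.** MD is confirmed by qPCR in blood or CSF. Then: "For other invasive bacterial infections, the reference standard test is positive culture or qPCR of bacterial pathogen from a sterile body site (blood/CSF"). Again either method suffices.
- **Statistical analysis, Primary.** PCT is assessed "in the diagnosis of early invasive bacterial infection against the reference standard of positive culture from a sterile site (blood/CSF"). Only culture is named. The first co-primary, in the same list, is assessed "in the diagnosis of early MD against the reference standard (qPCR) for" *N. meningitidis* DNA.

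The Objectives section gives the target of the second co-primary only as "in the diagnosis of Invasive bacterial infection" and does not say whether MD is included.

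**The concern.** A diagnostic accuracy estimate is determined by which children are placed in the diseased and non-diseased columns. For this co-primary the article gives two answers. Under culture or qPCR of any pathogen, every child with confirmed MD is a case. Under culture alone, a child whose MD is confirmed only by qPCR moves to the non-diseased column.

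A child moved in this way with a high PCT is scored as a false positive, although the test was right. One with a low PCT is scored as a true negative, although the test missed invasive disease. The first error lowers specificity and PPV; the second flatters NPV. The same would happen to a pneumococcal or *H. influenzae* infection found only by the routine blood PCR described in the Procalcitonin procedures.

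A second, smaller matter follows. By its description ("LAMP-MD is a rapid molecular amplification test for the detection of all serogroups of" *N. meningitidis* DNA), LAMP-MD addresses only the meningococcus, so in other invasive infections PCT is the only study point-of-care test that could flag the child. The listed analyses do not show PCT accuracy in that group separately.

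**Working it through.** **The plan's own figure.** The sample size formula gives 1.96² × 0.95 × 0.05 / 0.03² = 202.75, rounded up to 203, as stated. It concerns children negative on both tests and is unaffected by this point.

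**Placing one child.** Take a child with positive *N. meningitidis* qPCR in blood, negative cultures, and PCT above the study threshold of 1.93 ng/ml.

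| Rule applied | Status | PCT result scored as |
|---|---|---|
| First co-primary (qPCR) | case | true positive |
| Second co-primary, Methods/design (culture or qPCR) | case | true positive |
| Second co-primary, Statistical analysis (culture) | non-case | false positive |

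**Inputs for the size.**
- From the article: PCT sensitivity 0.89 and specificity 0.74 for early MD (Background, Procalcitonin); 300 children less 10% for refusal and dropout = 270.
- Assumed: 8 non-meningococcal invasive infections, all culture-positive; MD counts of 13, 20 or 40, where 40 is close to the article's 15% prevalence ceiling (0.15 × 270 = 40.5); 0.89 also holds in culture-negative MD; 0.74 holds in children without invasive infection. The share of MD that is culture-negative is not given, so one half and all are both shown.

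**Specificity.** Let k be the number of culture-negative MD children and N₀ = 270 − MD − 8 the children truly without invasive infection.

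Apparent specificity = (0.74 × N₀ + 0.11 × k) / (N₀ + k), so the fall is 0.63 × k / (N₀ + k).

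| MD | N₀ | k = half of MD | k = all MD |
|---|---|---|---|
| 13 | 249 | 0.724 | 0.709 |
| 20 | 242 | 0.715 | 0.692 |
| 40 | 222 | 0.688 | 0.644 |

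For example, with MD = 20 and k = 20: (242 × 0.74 + 20 × 0.11) / 262 = (179.08 + 2.20) / 262 = 0.692.

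**PPV, for MD = 20.** Assume also a PCT sensitivity of 0.50 in the 8 other infections. PCT positives number 242 × 0.26 + 20 × 0.89 + 8 × 0.50 = 62.92 + 17.80 + 4.00 = 84.72 under any definition.
- MD counted as cases: (17.80 + 4.00) / 84.72 = 0.26.
- Half of MD moved to non-cases: (8.90 + 4.00) / 84.72 = 0.15.
- All MD moved: 4.00 / 84.72 = 0.05.

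**NPV, for MD = 20.** PCT negatives number 270 − 84.72 = 185.28. With MD as cases, false negatives are 2.20 + 4.00 = 6.20 and NPV is 0.967. With all MD moved, false negatives are 4.00 and NPV is 0.978.

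**Precision of a non-meningococcal row.** With 8 cases of which 4 are detected, the exact 95% interval for sensitivity is 0.16 to 0.84.

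**The case against.** The strongest reply is that the definition is already clear. The word *other* in Reference standards follows the MD paragraphs and most naturally means invasive infections besides MD, which implies that MD is one of them. That agrees with the abstract and with Methods/design. The culture-only phrase may be shorthand in a condensed article, and the full protocol or analysis plan may spell the rule out. The first half of this stands: the inclusive reading is the more natural one, and no section says outright that MD children belong among the non-cases. But the culture-only wording sits in the section that fixes the analysis, and it contradicts two other sections of the same text. That is more than detail left to another document.

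A reader might also infer that including MD is itself a mistake, that the second co-primary then largely repeats the PCT-for-MD result, and that PCT accuracy in other infections will never be reported. The document does not support this.
- PCT against any invasive bacterial infection is a legitimate target. It fits the article's stated role for point-of-care tests of stratifying risk of invasive disease.
- Repetition depends on the MD share of cases, which is not given. With 40 cases, and assumed sensitivities of 0.89 for MD and 0.50 for the rest, an MD share of 20%, 50%, 80% or 90% gives pooled sensitivity 0.58, 0.70, 0.81 or 0.85. Only the last two are close to 0.89. If PCT performs equally well in both groups, pooling hides nothing in sensitivity.
- A breakdown by pathogen is something an article commonly leaves to the full plan, so its absence here does not show that it will not be done.

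**Conclusion.** The point holds as an inconsistency in the case definition of a co-primary outcome. Three sections support an inclusive definition by culture or qPCR, and the Statistical analysis section names culture only. Applied literally, that wording makes qPCR-confirmed, culture-negative MD children non-cases and biases PCT specificity and PPV downward.

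In the illustration the loss of specificity runs from about 2 points (13 MD children, half culture-negative) to about 10 points (40, all culture-negative). The PPV loss can be larger. These figures rest on the assumed case mix and on carrying the article's 0.89 and 0.74 over to these groups. If every MD case were also culture-positive, there would be no bias from this source. The direction is firm for any culture-negative MD, as long as PCT is positive more often in those children than in children without invasive infection.

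The missing separate figure for non-meningococcal infection is a useful addition to make, not an error in the plan.

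**What to change.** 1. In Statistical analysis, define invasive bacterial infection for the second co-primary as positive culture or qPCR of any bacterial pathogen from blood or CSF, and say that confirmed MD is included.
2. Align the other two sections. Methods/design should name the sterile site for the second part of its gold standard. Reference standards should say that its *other* infections, together with confirmed MD, make up the target of the second co-primary.
3. Add a descriptive secondary row, not at co-primary level: PCT accuracy for non-meningococcal invasive infection, with MD children removed from both cases and comparator, and with exact confidence intervals.

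The cost is a few sentences and one table row. The data are already being collected and the sample size does not change. The downside of the extra row is imprecision: with about 8 cases it could neither establish nor exclude poor PCT sensitivity, and the report should say so.

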### Sample size justification

We have calculated that we need 203 test negative patients (negative LAMP & low procalcitonin) to estimate a negative predictive value (NPV) of 95% or greater with confidence intervals of +/− 3% (Calculation below). Disease prevalence is estimated at 15% or lower, based on preparatory work in our centre and other epidemiologic studies, and we anticipate a combined refusal of consent and dropout rate of 10%. We therefore aim to recruit a total of 300 patients to achieve this. We have chosen to focus on NPV because with possible MD the emphasis is on exclusion of a life-threatening infection and as such and test or CPG must have a high NPV.

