#### Procalcitonin

0.5 ml of blood is taken from the samples collected as part of routine care. POCT PCT testing is done on this sample in the ED using the Samsung IB-10 analyser with a positive threshold level of > 1.93 ng/ml. If insufficient blood is obtained, then routine testing is prioritised. Routine blood testing includes WBC, CRP, coagulation screen, blood gas, and molecular testing for *N. meningitidis*, human enteroviruses, and other viral and bacterial targets (including *Streptococcus pneumoniae* and *Haemophilus influenzae*) using reference-laboratory real-time PCR methods – Fig. 2.

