### Potential bias

As the clinical team are not blinded to the results of the index tests, there is an increased risk of bias in treatment. It was deemed ethically unacceptable to withhold these results from clinicians. However as our performance accuracy is primarily assessed laboratory tests we expect any bias to be minimized, with a residual risk remaining for cases which require a clinical decision as to the likelihood of MD in the context of negative laboratory tests. When this occurs bias will be minimized by ensuring the treating clinician is not part of this panel, with information taken solely from clinical notes. In addition the laboratory team performing reference tests will be blinded to index tests. This includes blood culture testing and qPCR for other invasive bacterial infections.

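### The co-primary analysis of procalcitonin for invasive bacterial infection is set against culture only, while the reference-standard text says culture or qPCR

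*Protocol article*

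**What the plan says.** The second co-primary outcome is the accuracy of point-of-care PCT for invasive bacterial infection (IBI). The protocol states the reference standard for it in several places:

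- **Statistical analysis (Primary):** PCT is assessed "against the reference standard of positive culture from a sterile site (blood/CSF"). qPCR is not mentioned, although the item just before it names qPCR as the standard for meningococcal disease (MD).
- **Reference standards:** for invasive bacterial infections other than MD, "the reference standard test is positive culture or qPCR of bacterial pathogen from a sterile body site (blood/CSF").
- **Methods/design:** the gold standard includes "confirmation of an invasive bacterial infection through positive culture or qPCR of a bacterial pathogen".
- **Potential bias:** after stating that the laboratory is blinded to the index tests, the text adds "This includes blood culture testing and qPCR for other invasive bacterial infections".

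Two further places bear on whether the difference matters. Under Performing index tests, the Procalcitonin paragraph lists molecular testing of blood for *N. meningitidis*, *S. pneumoniae*, *H. influenzae* and other targets as routine, "using reference-laboratory real-time PCR methods". For MD itself the standard is qPCR of blood or CSF: "A positive reference standard test will be used to give a diagnosis of “confirmed MD".

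**The concern.** The reference standard decides which children enter the diseased column of the 2x2 table, and here a co-primary table has two definitions. An analyst who follows the analysis section and one who follows the reference-standard section would build different tables from the same data. They differ on the children whose culture is negative and whose qPCR is positive. Such children can be observed, because bacterial PCR on blood is part of routine care.

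Under the culture-only wording these children move to the uninfected column. A high PCT in such a child is then a false positive, and a low PCT is a true negative. The first lowers PPV, and also lowers specificity whenever PCT is positive more often in these children than in the truly uninfected. The second raises NPV, so PCT would look safer for ruling out infection than it is.

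**Working it through.** **The plan's own figure.** The sample-size formula reproduces: 1.96² × 0.95 × 0.05 / 0.03² = 202.75, rounded up to 203. It contains no term for the choice of reference standard, so neither 203 nor the target of 300 changes with the fix.

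**Comparing the statements.** Three sections (Methods/design, Reference standards, Potential bias) treat qPCR as a reference test for IBI. One (Statistical analysis) does not, and it is the one that specifies the co-primary comparison. No sentence says that culture-only is a deliberate restriction, or that one section takes precedence.

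**Illustrating the consequence of the literal reading.** Inputs:

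- Analysed: 300 less 10% refusal and dropout = 270 (Sample size justification).
- Prevalence: 15%, the upper limit given there, and 5% as an assumed lower value. That section does not say whether its figure is for MD or IBI.
- PCT sensitivity 0.89 and specificity 0.74 (Background, Procalcitonin). These are reported for early MD and are borrowed here for IBI.
- Share *f* of true cases that are culture-negative and qPCR-positive: not in the document. Values of 25%, 50% and 75% are assumed.
- PCT result independent of culture status among true cases: assumed.

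With D true cases and H = 270 − D uninfected children, the culture-only table is:

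- TP = 0.89·D·(1 − f)
- FN = 0.11·D·(1 − f)
- FP = 0.26·H + 0.89·f·D
- TN = 0.74·H + 0.11·f·D

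Worked case, 15% prevalence and f = 0.5: D = 40.5 and H = 229.5.

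- TP = 18.02, FN = 2.23, FP = 59.67 + 18.02 = 77.69, TN = 169.83 + 2.23 = 172.06.
- PPV = 18.02/95.72 = 0.188, against 36.05/95.72 = 0.377 on culture or qPCR.
- Specificity = 172.06/249.75 = 0.689, against 0.740.
- NPV = 172.06/174.29 = 0.987, against 169.83/174.29 = 0.974.

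| Prevalence | f | Children recoded (about) | Specificity | PPV | NPV |
|---|---|---|---|---|---|
| 15% | 0 | 0 | 0.740 | 0.377 | 0.974 |
| 15% | 25% | 10 | 0.713 | 0.282 | 0.981 |
| 15% | 50% | 20 | 0.689 | 0.188 | 0.987 |
| 15% | 75% | 30 | 0.666 | 0.094 | 0.994 |
| 5% | 0 | 0 | 0.740 | 0.153 | 0.992 |
| 5% | 25% | 3 | 0.732 | 0.114 | 0.994 |
| 5% | 50% | 7 | 0.724 | 0.076 | 0.996 |
| 5% | 75% | 10 | 0.716 | 0.038 | 0.998 |

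The numbers of PCT-positive and PCT-negative children do not change, so under these assumptions PPV and 1 − NPV are each multiplied by (1 − f). Sensitivity stays at 0.89 only because of the independence assumption. If PCT positivity differed by culture status, sensitivity would move too.

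**The case against.** The best defence is that the analysis sentence is a drafting slip. Reference standards is the section dedicated to this definition, and two other sections agree with it, so an analyst might well use culture or qPCR anyway. That is plausible, and it means the error is conditional: a reader might infer that the co-primary result will be biased, but the document does not establish which definition will be applied. The defence does not remove the need to correct the sentence, since the text that specifies the analysis says culture only.

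Three other limits stand.

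- **NPV.** A reader might infer that the inflated NPV is the one the study was sized on. It is not. Sample size justification asks for precision on an "negative predictive value (NPV) of 95% or greater" in children negative on both tests ("we need 203 test negative patients (negative LAMP & low procalcitonin")), and gives possible MD as the reason. The estimate affected here is PCT alone for IBI. In the worked case its NPV shifts by 1.3 points (0.974 to 0.987), less than the planned half-width of 3 points.
- **The MD definition.** A reader might go further and want a positive culture of *N. meningitidis* to count as confirmed MD. The protocol consistently uses qPCR for MD, and sends unclear or clinically probable qPCR-negative cases to a committee blinded to the point-of-care results. Adding culture would be a design preference, not the repair of a contradiction.
- **MD within IBI.** The sentence in Reference standards covers infections other than MD, so how MD cases enter the IBI analysis is left unstated. A culture-negative child with qPCR-confirmed MD would be diseased in one co-primary analysis and uninfected in the other only if the culture-only wording is applied to all children.

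**Conclusion.** The point holds as an unreconciled contradiction in the reference standard of a co-primary outcome. It is more than clerical, because the two wordings give different 2x2 tables whenever a culture-negative, qPCR-positive child is enrolled. The direction under the literal reading is clear: PPV falls and NPV rises. Specificity also falls if PCT is positive more often in the recoded children than in the uninfected.

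The size cannot be determined from the document. The figures above rest on an assumed culture-negative share, on accuracy values reported for MD, and on independence of PCT and culture status. Across the table PPV loses between a quarter and three quarters of its value, simply following the assumed share. The absolute changes in specificity and NPV are modest, and smaller still at 5% prevalence. The contradiction itself depends on none of these assumptions.

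**What to change.** In the second primary item of Statistical analysis, insert qPCR of a bacterial pathogen as an alternative to positive culture, keeping the restriction to blood or CSF, so that the item matches Methods/design and Reference standards. Add one sentence stating that qPCR-confirmed MD counts as IBI in that analysis. Leave the definition of confirmed MD as it is.

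The cost is one amended sentence and one new one. No extra samples or tests are needed, because bacterial PCR on blood is already described as routine, and the sample size is unaffected. The change should be made and dated before the data are analysed, so that the choice of reference standard cannot follow the results.
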